### Study population and sample size calculation

Patients planned for bilateral cataract surgery without visual acuity influencing comorbidities are eligible for study participation. The surgical procedures can be performed on the same day (i.e. immediate sequential) or on two different days. Exclusion criteria are: cataract surgeries combined with other procedures (including keratoplasty, vitrectomy, glaucoma filter implants), presence of ocular comorbidities that negatively influence post-operative visual acuity (such as amblyopia, age-related macular degeneration, diabetic retinopathy, glaucoma or uveitis), insufficient command of the Dutch, German or English language, no access to a smartphone and computer/tablet, and inability to successfully perform the demo version of the web-based eye exam.

The sample size calculation is based on determining the validity of the web-based eye exam since calculations based on cost-effectiveness and safety were not feasible. We aim to assess whether the corrected distance visual acuity obtained with the web-based refraction is not significantly worse than the visual acuity obtained with the manifest refraction. We assume no difference between the measurements and consider a difference up to 0.10 logMAR to be non-inferior. With a standard deviation of 0.30 logMAR (a commonly used SD in power calculations on visual acuity [29–31]), an α of 0.05, a power of 90, 20% loss to follow-up and using a one-sided, one sample t-test, 94 eyes are then required in the telemonitoring group (so 47 participants, as all measurements will be performed bilaterally). This results in a total study population of 94 participants (188 eyes) for both study groups.

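### On the plan's own inputs, 94 eyes with 20% loss leave about 75 evaluable eyes and about 88–89% power, slightly short of the stated 90%

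*Protocol article*

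**What the plan says.** The calculation is in the protocol article, Methods, under Study population and sample size calculation. It concerns the comparison, within the telemonitoring group, of corrected distance acuity obtained with the web-based refraction and with the manifest refraction. The stated inputs are:

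- true difference: "We assume no difference between the measurements"
- margin: "consider a difference up to 0.10 logMAR to be non-inferior"
- spread: "With a standard deviation of 0.30 logMAR"
- error rate and test: "an α of 0.05", "using a one-sided, one sample t-test"
- power of 90%, and "20% loss to follow-up"

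From these the plan arrives at 94 eyes ("a power of 90, 20% loss to follow-up and using a one-sided, one sample t-test, 94 eyes are then required"), that is 47 participants with both eyes measured, in the telemonitoring group. It then doubles this for 1:1 allocation: "This results in a total study population of 94 participants (188 eyes) for both study groups". It gives neither the number of eyes needed before loss nor the way the loss was added.

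**The concern.** When a fraction d of those enrolled is expected to be lost, the evaluable number must be divided by (1 − d). Multiplying by (1 + d) adds too few, because the loss then falls on the enlarged number. Here 94 less 20% is about 75, which is below the number the stated inputs need for 90% power. The three figures in the sentence (94 eyes, 20% loss, 90% power) therefore cannot all be true.

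The stake is modest. This is the only sample size justification in the article, which says that calculations for cost-effectiveness and safety were not feasible, so readers will take its power figure at face value. The figure also carries into the total for both groups. No analysis or estimand depends on it.

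**Working it through.** **Inputs**, all from the sample size paragraph: margin Δ = 0.10, true difference 0, SD σ = 0.30, one-sided α = 0.05, power 90%, loss 20%, one-sample test. Eyes are counted as independent, as the plan counts them.

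**1. Evaluable eyes needed.**
- Normal approximation: n = [(z₀.₉₅ + z₀.₉₀) × σ/Δ]² = (1.645 + 1.282)² × (0.30/0.10)² = 77.07, so 78.
- One-sided one-sample t-test (noncentral t): 79. Power is 90.2% at 79 and 89.8% at 78.

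**2. Reproducing the plan's 94.**

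| Evaluable n | n × 1.2 | n / 0.8 |
|---|---|---|
| 78 (normal) | 93.6, so **94** | 97.5, so 98 |
| 79 (t-test) | 94.8, so 95 | 98.75, so 99 |

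Only 78 × 1.2 returns exactly 94. Other settings were tried. The nearest with correct inflation is one-sided α = 0.025 with 80% power, which gives 73/0.8 = 91.25, so 92 eyes, but it contradicts both the stated alpha and the stated power.

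**3. What 94 eyes deliver after 20% loss.** 94 × 0.8 = 75.2 eyes. In participants, 20% of 47 is 9.4. Losing 10 leaves 37 (74 eyes) and losing 9 leaves 38 (76 eyes).

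| Evaluable eyes | Power, t-test | Power, normal |
|---|---|---|
| 74 | 88.4% | 88.9% |
| 75 | 88.8% | 89.3% |
| 76 | 89.2% | 89.6% |

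No entry reaches 90%.

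**4. Loss that 47 participants can bear at 90% power.**
- Lose 7 (7/47 = 14.9%): 40 participants, 80 eyes, 90.5% by t-test.
- Lose 8 (8/47 = 17.0%): 39 participants, 78 eyes, 89.8% by t-test, 90.3% by the normal approximation.

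With the named t-test and loss of whole participants, the allowance is therefore about 15%. A 16% allowance just fails even if eyes are counted singly: 94 × 0.84 = 78.96, under 79.

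**5. Size with the loss divided out.** 98 eyes is 49 participants, and 99 eyes rounds up to 50. For both groups that is 98 to 100 participants, against the stated 94. The shortfall in the telemonitoring group is 4–5 eyes, or 2–3 participants.

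**The case against.** - **The gap is too small to matter.** By t-test at 75 eyes it is 1.1 points, and by the normal approximation 0.7. An SD of 0.293 instead of 0.30 would restore 90% at 75 eyes by t-test, and the plan presents 0.30 only as a value commonly used in such calculations. This stands, and it is why the point is minor. It does not make the printed sentence correct.
- **The multiplication by 1.2 is not shown.** This also stands. The exact match needs the normal-approximation 78, while the named t-test with the same step gives 95. A reader might infer that the authors demonstrably multiplied by 1.2; the article supports only that 94 is consistent with it. The inconsistency does not depend on how 94 was reached.
- **94 might be the evaluable number.** The wording does not allow this. The 20% loss is listed among the inputs that lead to 94, and 94 becomes the 47 participants to be enrolled. Without any loss, 94 eyes would give 94.1% power, not 90%.
- **Losses are limited or replaced.** Under Recruitment and informed consent procedure, the demo version is meant to limit loss after enrolment, and participants who miss the baseline questionnaires or web exam are replaced. This makes a real shortfall less likely. It does not cover those lost between baseline and the comparison at 4–6 weeks, and it does not change the stated 20%.

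**Conclusion.** This is a minor error, wrong as written. On the plan's own inputs, 94 eyes with 20% loss give about 88–89% power (88.4–89.2% by t-test, 88.9–89.6% by the normal approximation) rather than 90%. Equivalently, 94 eyes support 90% power by t-test with about 15% loss rather than 20%.

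A reader might infer that the trial is materially underpowered or must enrol more participants. The document does not support that: the gap is about one point and smaller than the uncertainty in the assumed SD.

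All figures rest on the stated SD, margin and zero difference, and on treating the two eyes of a participant as independent. Correlation between fellow eyes would change the power, but that is a separate point and adds no weight to this one.

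**What to change.** Restate the sentence and leave enrolment unchanged. Either version would do:

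- *47 participants (94 eyes) with 20% loss leave about 75 evaluable eyes and about 89% power*; or
- *90% power allowing for about 15% loss (7 of 47 participants, leaving 80 eyes)*.

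It would also help to print the evaluable number (79 by t-test, 78 by the normal approximation) and how loss was added, so that a reader can follow the step. If the calculation is ever redone to allow for correlation between fellow eyes, the result of that recalculation should replace these figures.

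The cost is one sentence and a slightly less favourable power or loss allowance. Design, conduct and analysis are unaffected.

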### Statistical analysis

Data will be collected and analyzed preoperative (i.e. at baseline) and at three postoperative time points. All quantitative variables will be summarized. The data will be tested for distribution, and if not normally distributed the corresponding non-parametric test will be used. For all analyses, a *P* < .05 is considered statistically significant.

Comparisons between the web-based eye exam and the conventional clinical assessments will be analysed according to the Bland-Altman methodology [32]. We will compare assessments of distance visual acuity, near visual acuity and refractive error. Furthermore, we will analyse independent associations between clinical characteristics and agreement between the web-based exam and the conventional reference tests. Safety of the remote follow-up will be evaluated by comparing the occurrence of adverse events in both study groups. The cost-effectiveness will be assessed by QALYs, total costs, and the probability of adverse events and additional clinical examinations.

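### The 90% power for the primary non-inferiority test counts fellow eyes as independent; on the plan's own inputs it falls to about 70–80% at plausible between-eye correlations

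*Protocol article*

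**What the plan says.** The protocol article bases the trial's size on the validity objective alone (Study population and sample size calculation). The quantity tested is the difference, in the same eye, between corrected distance acuity with the web-based prescription and with the manifest prescription. The inputs are:

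- Assumed truth: "We assume no difference between the measurements".
- Margin: "consider a difference up to 0.10 logMAR to be non-inferior".
- Spread: "With a standard deviation of 0.30 logMAR (a commonly used SD in power calculations on visual acuity".
- Error rate, power and loss: "an α of 0.05, a power of 90, 20% loss to follow-up".
- Test: "using a one-sided, one sample t-test".

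The result is that "94 eyes are then required in the telemonitoring group (so 47 participants, as all measurements will be performed bilaterally", and 94 participants over both groups. No between-eye correlation or design effect is mentioned.

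The Statistical analysis section says that "Comparisons between the web-based eye exam and the conventional clinical assessments will be analysed according to the Bland-Altman methodology". It names no unit of analysis and does not say how two eyes of one person are handled.

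**The concern.** A one-sample t-test formula needs independent observations. Turning 94 eyes into 47 people by halving is valid only if the differences in fellow eyes are uncorrelated.

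The article gives reason to expect otherwise. One person performs the home refraction of both eyes unsupervised. The article also treats digital proficiency as a characteristic of the person: a demo screens for it (Recruitment and informed consent procedure), and the age strata rest partly on age-related digital literacy (Randomization). Such a factor would act on both eyes.

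This is the primary objective and the only basis for the sample size. If correlation is handled in the analysis, the trial has a greater chance than planned of failing to show non-inferiority. If it is ignored, the trial has a greater chance than 5% of claiming non-inferiority wrongly.

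**Working it through.** **1. Reproducing the plan's figure.** With SD 0.30, margin 0.10, true difference 0, one-sided alpha 0.05 and 90% power:

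n = [0.30 × (1.645 + 1.282) / 0.10]² = 77.1, so 78 eyes.

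Adding 20%: 78 × 1.2 = 93.6, so 94 eyes. This matches exactly. (The exact t calculation gives 79 eyes, and 95 after inflation. Dividing 78 by 0.8 gives 98, which does not match.) The match leaves no room for a correlation term.

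**2. Participants left after loss.** 47 × 0.8 = 37.6, taken as 38 participants (76 eyes).

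**3. Participant-level test.** Take the mean of the two eyes' differences for each person. Its SD is 0.30 × √((1 + rho)/2). Power comes from the non-central t distribution with 37 degrees of freedom and non-centrality 0.10 × √38 / SD. The article gives no rho, so a range is shown.

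| rho (assumed) | SD of participant mean | Power, 38 evaluable | Power, all 47 retained | Evaluable participants for 90% |
|---|---|---|---|---|
| 0 | 0.212 | 88.6% | 93.8% | 40 |
| 0.3 | 0.242 | 80.4% | 87.4% | 52 |
| 0.5 | 0.260 | 75.3% | 83.0% | 60 |
| 0.7 | 0.277 | 70.6% | 78.7% | 67 |

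With 37 evaluable participants instead of 38, power is 79%, 74% and 70% at rho 0.3, 0.5 and 0.7.

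The first row separates the causes. At rho 0 the power is already 88.6%, so 90 − 88.6 = 1.4 points come from multiplying by 1.2 instead of dividing by 0.8 and from fewer degrees of freedom. The rest is correlation: about 8, 13 and 18 points.

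**4. Eye-level test, as the alternative.** Suppose the one-sample t-test is applied to 76 eyes as if independent. The standard error is then too small by the factor 1/√(1 + rho). At a true difference equal to the margin, the one-sided error is approximately 1 − Φ(1.645/√(1 + rho)), which is 7.5%, 9.0% and 10.4% at rho 0.3, 0.5 and 0.7. Simulation with 38 participants (200,000 runs) gives about 7.4%, 9.0% and 10.5%. The simulated power of this test at a true difference of 0 is about 86%, 85% and 83%.

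Steps 3 and 4 describe different analyses. The first keeps the error at 5% and loses power; the second loses less power because it exceeds 5%.

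**5. Sensitivity to the SD.** At rho 0.5 with 38 participants, an SD of same-eye differences of 0.24 gives 89.7% power. An SD of 0.20 gives about 92% even at rho 1.

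**The case against.** **The final analysis may handle clustering.** The article condenses a fuller protocol, and an analysis plan may exist. The t-test is named only as the sizing formula, and Bland-Altman methodology does not exclude limits that account for two eyes per person. A reader might infer that the trial will analyse eyes as independent and so exceed its 5% error rate. The article does not say so, and its silence on the model is not a fault. The error figures therefore stay conditional. This does not rescue the power: no choice of model makes 90% true for these inputs at a material positive rho.

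**The real trial may be adequately powered.** The SD of 0.30 is presented as a common value for visual acuity, not as the SD of a difference between two readings of the same eye. If the latter is smaller, power may well reach 90%. This stands. A reader might infer that the trial is underpowered in fact; the document supports only that the calculation does not deliver 90% on its stated inputs.

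**The correlation is assumed.** The article does not say that fellow eyes share a room or an examiner. Surgery may fall on two different days. The endpoint is read on a hospital chart, so home conditions reach it only through the web-based prescription. This also stands: positive correlation is plausible, not shown, and near rho 0 the shortfall almost vanishes. But independence is an assumption too, and the article neither states nor defends it.

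**Conclusion.** The concern holds for the calculation as written. The multiplication is correct, but the independence assumption behind it is unstated. For rho 0.3 to 0.7 at SD 0.30, a participant-level test with 38 evaluable participants has about 70–80% power against 90% stated, with about 1.4 points of that gap due to the loss inflation and degrees of freedom. Even with no loss at all, power at these values of rho is 79–87%.

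It would be wrong to combine that power loss with the raised error of 7.4–10.5%, since each belongs to a different test. The size rests on an assumed rho and on taking the plan's SD as the SD of same-eye differences; the direction holds for any positive rho.

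**What to change.** - State that the primary non-inferiority test takes the participant as cluster, using either a random participant intercept or the mean of the two eyes. Compute the Bland-Altman limits on the same basis, with between- and within-participant variance.
- State the assumed between-eye correlation. Then either restate the power of 47 telemonitoring participants as about 70–80% for rho 0.3–0.7 at SD 0.30, or state and justify a smaller SD of same-eye differences that supports 90% (about 0.24 at rho 0.5).

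The cost is a change of wording and a less favourable stated power. Recruitment and visits do not change. If a fuller protocol or analysis plan already clusters by participant, only the power statement needs revision.

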### Study procedures

A flowchart describing the study procedures is depicted in Fig. 1.

**Fig. 1 Fig1:**
[figure not shown]
Flowchart of the CORE-RCT study procedures. Overview of study procedures: recruitment, randomization and study measurements

#### Recruitment and informed consent procedure

Eligible patients will be identified by the ophthalmologist or delegated personnel at the outpatient department, when cataract is diagnosed and the cataract surgery will be planned for both eyes. All eligible patients will be provided with written information about the study. Patients who are interested to participate, will be invited to perform a demo version of the web-based eye exam at home. We always recommend assistance by a relative. The demo contains the home set-up phase and a shortened test flow, and aims to assure that the technical requirements and a sufficient level of digital proficiency for study participation are met, preventing a high loss-to-follow-up after enrolment. Patients who fail to access the demo version of the web-based eye exam, will be excluded from randomization. To report on this participation bias, we will keep track of an overview of all invited patients and record reasons for non-participating.

If all inclusion criteria are met and the patient is willing to participate, written informed consent will be obtained. After enrolment, participants can leave the study at any time for any reason if they wish to do so. Participants who have not completed the questionnaires and/or performed the web-based eye exam prior to surgery (i.e. at baseline) will be withdrawn from the study and replaced.

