#### Patients’ perspective

Firstly, we will determine if remotely self-assessing vision influences patient-reported outcome measures of visual function (Catquest-9SF and NEI-VFQ-25 questionnaires [22, 23]) and quality of life (EQ-5D-5L questionnaire [24]), by comparing the outcomes between both randomization groups.

Secondly, we will evaluate the user experiences with the web-based tool by a custom quantitative questionnaire, distributed amongst the participants of the telemonitoring group at the end of the study. This questionnaire is based on the theoretical Technology Acceptance Model; a commonly used model to evaluate and incorporate user experiences in the development process of technology. Since its introduction by Davis in 1989 [25], the model has been extended by multiple research teams, including for utilization in health care settings [26–28]. We used the extended models as a reference framework and developed a study-specific questionnaire in cooperation with the University of Twente, the Netherlands (Additional file 1). Lastly, the quantitative results are enriched with in-depth qualitative interviews (Additional file 2). Dutch-speaking participants of the telemonitoring group will be invited to report on their experiences with the web-based eye exam. Interviews will be conducted by researchers experienced in qualitative interview studies, until data saturation is reached (i.e. when no longer new insights are gained).

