#### Study measurements

The ‘telemonitoring’ group will have a post-operative follow-up involving web-based eye exams, digital questionnaires and telephone consultations. The invitations for the web-based eye exams and questionnaires will be sent via e-mail at 4 specific time points: prior to surgery, < 1 week after the surgery, 4-6 weeks after the surgery and 3 months after surgery. Prior to surgery, visual acuity will be assessed with the participant’s current spectacles, if applicable. After surgery, the web-based eye exam will be performed without spectacles. In addition, participants will fill out triage questionnaires to identify any (alarming) symptoms.

Shortly (1-7 days) after surgery, uncorrected distance visual acuity (UDVA) will be assessed remotely, and a telephone consultation will take place if deemed necessary by the surgeon. Approximately 1 month (i.e. 4-6 weeks) after surgery, the web-based tool will assess uncorrected visual acuity (distance and near) and the residual refractive error. After performing this remote assessment at home, participants will have an in-hospital ophthalmic examination with conventional visual acuity and refraction assessments for validity and safety purposes. The observer and participant will be blinded for the web-based refraction outcome during the manifest refraction. At this in-hospital consultation, distance visual acuity will be assessed by an ETDRS chart at 4 m, both uncorrected (UDVA) and corrected (CDVA). The CDVA will be assessed twice: using both the prescriptions of the web-based and the manifest refraction. Near visual acuity will be assessed uncorrected using a Sloan ETDRS chart at 40 cm. Three months after surgery, the web-based assessment will be repeated and participants will be requested to fill out a questionnaire about their experiences with the web-based eye exam. In addition, a sample of the Dutch-speaking participants will be interviewed to further explore their perspective on remote follow-up after cataract surgery.

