The ‘usual care’ group will have a post-operative follow-up adhering to the clinic’s usual practice. Typically, regular consultations will be planned within 1 week after surgery (i.e. short-term evaluation) and at approximately 4-6 weeks after surgery (i.e. long-term evaluation). The latter will include a full ophthalmic examination and refraction assessment, to assess post-operative visual outcomes and residual refractive errors. In some of the participating centres, the short-term follow-up evaluation will be a telephone consultation instead of an in-hospital consultation, or no consultation at all, depending on the standard guidelines of this clinic.

For both study groups, all adverse events and additional consultations - at other moments than the specified time points in the study flow chart - will be registered. Prior to (i.e. at baseline) and 3 months after surgery, participants of both groups will be requested to fill out questionnaires about quality of life (EQ-5D-5L [24]) and visual function (Catquest-9SF [22], NEI-VFQ-25 [23]). Three months after surgery, all participants will be requested to fill out a short custom questionnaire about expenditures related to hospital visits (such as costs for transportation and parking).

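### The rule that withdraws and replaces participants without a baseline web exam appears to remove randomised people from the telemonitoring arm only, and so can bias the between-arm comparisons

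*Protocol article*

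**What the plan says.** The protocol article sets two hurdles in Recruitment and informed consent procedure. The first is the home demo: "Patients who fail to access the demo version of the web-based eye exam, will be excluded from randomization". The second comes after enrolment and concerns baseline data: "Participants who have not completed the questionnaires and/or performed the web-based eye exam prior to surgery (i.e. at baseline) will be withdrawn". Read to its end, the same sentence also provides for replacement of those who have not "performed the web-based eye exam prior to surgery (i.e. at baseline) will be withdrawn from the study and replaced".

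Study measurements then describes each arm in turn. The telemonitoring paragraph opens with "The ‘telemonitoring’ group will have a post-operative follow-up involving web-based eye exams, digital questionnaires and telephone consultations" and continues: "The invitations for the web-based eye exams and questionnaires will be sent via e-mail at 4 specific time points: prior to surgery". The usual-care paragraph follows clinic practice and lists no web exam. On baseline questionnaires the text covers both arms: "participants of both groups will be requested to fill out questionnaires about quality of life", and likewise for visual function.

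Several objectives compare the arms. Patient-reported outcomes are assessed "by comparing the outcomes between both randomization groups", and adverse events and the cost-effectiveness ratio are also compared between the groups. The main objective and the sample size concern a comparison within the telemonitoring arm.

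**The concern.** A person can miss an arm-specific baseline exam only after being allocated to that arm. If the web exam belongs to telemonitoring alone, the web-exam limb removes randomised telemonitoring participants and puts others in their place, while similar people allocated to usual care stay in. Randomisation then no longer fully protects the comparisons of adverse events, Catquest-9SF, NEI-VFQ-25, EQ-5D-5L and costs.

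The article gives reasons to doubt that non-completion is random. Randomization stratifies by age because of age-related digital literacy, and Background expects e-health to be harder for older people. The demo uses a shortened test flow, so passing it does not show that a person will complete the exam itself.

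The validity result is touched as well. Background says the unsupervised home setting is meant to resemble later real-world use. A sample from which people without a first exam have been replaced is narrower than that.

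An analysis plan could not fully repair this. In its ordinary meaning, withdrawal from the study before surgery ends data collection, so the later outcomes of those people would not exist to be analysed.

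**Working it through.** **1. The plan's own figure.** Inputs from Study population and sample size calculation: SD 0.30, margin 0.10 logMAR, true difference 0, one-sided alpha 0.05, power 90%, 20% loss. n = (0.30 × (1.645 + 1.282) / 0.10)² = 77.07, so 78 eyes. 78 × 1.2 = 93.6, so 94 eyes, or 47 participants per arm. The stated figure is reproduced. The present point does not depend on it; 47 per arm is used only as a scale in step 5.

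**2. Which limb can act in which arm.**

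| Baseline item | Telemonitoring | Usual care |
|---|---|---|
| Demo (before randomisation) | required | required |
| Questionnaires | requested | requested |
| Web exam before surgery | "will be sent via e-mail at 4 specific time points: prior to surgery, < 1 week after the surgery" | none listed |

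The demo filters both arms equally. The questionnaire limb can remove people from either arm. Only the web-exam limb is one-sided as written.

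**3. Timing.** The only exclusion that the text places before randomisation is demo failure. An exam given to one arm must follow allocation, so the web-exam withdrawal would fall after it. This is an inference: no sentence states the order, and the flowchart is not shown.

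**4. Size of the bias.** Let w be the share of the telemonitoring arm removed and D the amount, in SD, by which those removed do worse than those kept. The mean of the whole arm is (mean of those kept) − w × D, so keeping only completers shifts the mean by w × D. If the questionnaire limb also removes people from usual care, the net bias is the difference between the two arms' products and can be smaller. The documents give neither w nor D. On assumed values, with no matching removal in usual care:

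| w | D = 0.2 | D = 0.5 | D = 0.8 | Withdrawn to retain 47 = 47w/(1 − w) |
|---|---|---|---|---|
| 5% | 0.01 | 0.025 | 0.04 | 2.5 |
| 10% | 0.02 | 0.05 | 0.08 | 5.2 |
| 20% | 0.04 | 0.10 | 0.16 | 11.8 |

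If D = 0, the bias is zero whatever the value of w.

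**5. What that does to a test.** With 47 per arm the standard error of a difference is √(2/47) = 0.206 SD. For a nominal two-sided 5% test with no true difference (normal approximation), the false-positive rate is 5.0% at a bias of 0.01 SD, 5.7% at 0.05, 7.7% at 0.10 and 12.1% at 0.16.

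**6. Completion.** As an illustration, suppose 15% are withdrawn at baseline and 20% of the rest are lost later. Primary data then come from 0.85 × 0.80 = 68% of the telemonitoring participants randomised, against 80% if only those retained are counted. The 15% is assumed, and the 20% is the plan's allowance for loss.

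**The case against.** The strongest reply is that the order is not settled. The rule stands in the recruitment section, ahead of Randomization, and speaks of participants without naming an arm. Both arms might be meant to do the baseline exam before allocation, and the missing flowchart might show it. This stands as a limit on certainty. It does not remove the need for a change, because Study measurements lists the exam for one arm only and the passages would still have to be reconciled.

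A reader might infer that the rule acts in telemonitoring alone and leaves usual care unfiltered. The text does not support that: missing questionnaires can lead to withdrawal from usual care too.

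A reader might also infer that every between-arm comparison is biased, in favour of telemonitoring. That goes too far. Non-completion has to occur, differ between arms and be related to the outcome. The common demo should reduce it. It happens before surgery, so it cannot be a response to post-operative results, and nothing in the article links a skipped pre-operative exam to surgical adverse events. The direction is an assumption.

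Nor do the documents show that tool failures will be hidden, or that a report would give 80%. A skipped exam need not be a tool failure, and a condensed article may leave participant flow to other documents. What can be said is that the promised log covers invited patients and reasons for not participating, and does not mention people withdrawn after enrolment.

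Finally, the main result is a within-arm comparison, and the article says that sizing on safety or cost-effectiveness was not feasible. That is fair, and it limits the consequence. Those comparisons are nevertheless stated objectives and the reason for having a randomised control arm.

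**Conclusion.** The point holds in a limited form. As written, one limb of the withdrawal rule appears to be a post-randomisation exclusion with replacement that acts in the telemonitoring arm only. It can bias the between-arm comparisons of adverse events, patient-reported outcomes and costs, and it narrows the validity sample to people who have already completed the baseline exam.

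The size cannot be fixed from the documents. It is 0.05 to 0.10 SD if 10 to 20% are removed and differ by 0.5 SD, up to 0.16 SD at the far end of the assumed range, and zero if those removed do not differ from those kept. At 0.10 SD the bias is about half the standard error of a comparison with 47 per arm: modest, but avoidable. The conclusion rests on the inferred order of allocation and baseline exam, on the reading that usual care has no web exam, and on non-completion being related to outcome.

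**What to change.** Choose one of two amendments.

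1. State that both arms complete the baseline questionnaires and the web exam before randomisation, so that non-completers are never randomised. Bring Study measurements into line with this.
2. Otherwise, delete withdrawal and replacement for randomised participants. Follow everyone randomised and analyse them by allocated arm for adverse events, patient-reported outcomes and costs. Allow extra enrolment only to keep up the validity sample.

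Under the second option, report baseline non-completion by arm, with the proportion of all randomised telemonitoring eyes that yielded a web refraction next to the non-inferiority result.

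The change is short. Under the first option, usual-care participants do one extra exam. Under the second, a few participants with incomplete data stay in the analysis and the tool's completion rate looks less favourable.
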